### Data collection

All efficacy parameters will be collected during hospitalization of the patient in the ICU. In case of hospital discharge, phone calls will be made by the investigators or the research team with at least three attempts to contact the patient, his/her physician, or the patient’s emergency contact in a period of 10 days at different times of the day. If there is no answer, vital statistics will be collected via contact of the town council of the patient’s birthplace.

Data will be collected by the investigators and their teams in an electronic case report form (e-CRF). Data will be monitored by a clinical research associate (CRA) and checked for consistency and missing values by a data manager.

### Randomization

Centralized blocked-balanced randomization, in a 1:1 ratio, will be computer-generated by the clinical research unit (URC-EST). Randomization will be stratified on center. Investigators are blinded to the block size.

### Statistical analysis

The study is designed to demonstrate the non-inferiority on the composite endpoint of mortality and recurrence at 90 days of the 8-day strategy versus the 15-day strategy for PA-VAP. Considering the mortality and/or recurrence of PA-VAP rate of 35.7% [7], 284 patients will be required in each group to achieve a power of 80% to exclude a 10% difference between the two groups with an α risk of 5%. To account for a possible 5% patient loss to follow-up, we planned to enroll 600 patients.

### Data analysis

Baseline characteristics of patients will be described per group. Qualitative data will be described with frequencies and percentages; quantitative data will be described with mean and standard error or with median, interquartile interval, and range. Since this is a non-inferiority study, analysis of principal criteria will be performed on a per protocol population. The per protocol population will be defined as randomized patients without major protocol deviations such as non-respect of all selection criteria, clear non-respect of the antibiotic duration allocated (+/– 24 hours), missing data for the primary endpoint, and major protocol deviation(s) identified during a blinded data review before data base freezing. Non-inferiority will be tested by a Dunnett and Gent chi-squared procedure [21]. Secondary analysis in an intent-to-treat (ITT) population will also be performed.

Secondary outcomes will be analyzed under a superiority assumption. Day 30 and day 90 mortality rates and acquisition of MDR pathogens during hospitalization in the ICU will also be compared between groups by a chi-squared test or a Fisher’s exact test, if the use conditions were not verified. Duration of mechanical ventilation, duration of hospitalization in the ICU, duration of exposure to antibiotics, and number of extrapulmonary infections during hospitalization in the ICU will be compared between groups by Student *t* tests or Mann-Whitney/Wilcoxon tests, if needed. Types of extrapulmonary infections will be described.

The association between respiratory colonization with yeast at diagnosis and PA recurrence will be studied by logistic regression adjusted on the randomization group. The association between monotherapy or combination therapy and mortality and PA recurrence will be studied by a logistic regression adjusted on the randomization group. Procalcitonin levels at days 0, 1, 3, and 7 will be described, and their prognosis values on mortality and *P. aeruginosa* recurrence will be studied by logistic regression and sensitivity and specificity analyses. Missing data will be not replaced.

The study will be conducted in accordance with the Helsinki Declaration and French laws and regulations. The study has received its approval from the French ethics committee (Comité de Protection des Personnes Ile de France VI) as well from the French Drug Safety Agency (Agence Nationale de Sécurité du Médicament et des Produits de Santé) (EudraCT 2015-003102-17).

All records and subjects’ identities will remain confidential in accordance with the following French regulations: the French National Committee of Informatics and Liberties and the French Consultative Committee for Data Processing in Health Research rules. The trial protocol was written following the Recommendations for Interventional trials (SPIRIT) Checklist (see Additional file 1).

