Antibiotic treatment should be started just after realization of bacteriological sampling, without waiting for the result. The choice of initial antibiotic therapy will be left to the discretion of the physician according to usual care based on the clinical context, previous antibiotic therapy, the presence or absence of risk factors for multidrug-resistant (MDR) pathogen antibiotics or hospitalization in the previous 90 days (current hospitalization ≥5 days, mechanical ventilation ≥5 days, support in a dialysis center or residency in a nursing home), local epidemiological data, and finally knowledge that the patient is already known as being colonized by a MDR pathogen. In these situations, a broad-spectrum antibiotic will be recommended immediately, with the association of a β-lactam/β-lactamase inhibitor or an antipseudomonal cephalosporin, and an aminoglycoside or an antipseudomonal fluoroquinolone for 3 to 5 days. An initial antibiotic with a narrow spectrum will be accepted in the face of early onset pneumonia (mechanical ventilation <5 days) and in the absence of risk factors for MDR pathogens and in accordance to the marketing authorization (AMM), contraindications, dosing recommendations, and drug interactions (http://base-donnees-publique.medicaments.gouv.fr/). Investigators are strongly encouraged to convert this initial regimen into a narrow-spectrum therapy, based on culture results. All antibiotics would be withdrawn, either at the end of day 8 or day 15, according to the randomization assignment, except those prescribed for a documented pulmonary infection recurrence or a new extrapulmonary infection before that day. The patient will be randomized just after antibiotic susceptibility test results and assigned to the SD arm or the LD arm. Screening of MDR pathogens will be realized with a surveillance culture of swab samples from the rectum for extended-spectrum β-lactam-producing Enterobacteriaceae (ESBL) and of swab samples from the anterior nares for methicillin-resistant *Staphylococcus aureus* (MRSA) at the patient’s admission in the ICU, and then once weekly until the patient’s discharge from the ICU (see Figs. 1 and 2).

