## Discussion

This study will investigate the influence of duration of antibiotic therapy on mortality and recurrence of PA-VAP. Our goal is to demonstrate that a short antibiotic therapy (8 days of effective antibiotic therapy) compared to a long antibiotic therapy (15 days of effective antibiotic therapy) is safe without excess mortality or recurrence, and decreases the duration of exposure to antibiotics and the acquisition of MDR pathogens. Furthermore, this study will evaluate the relationship between PA recurrence and (1) respiratory colonization with yeast at diagnosis, (2) treatment with monotherapy or combination therapy, and (3) procalcitonin levels during the course of VAP.

We believe that the present study has several strengths. First, it specifically addresses the issue of recurrence of PA-VAP, and the number of patients to be included (*n* = 600) has been calculated according to an expected rate of 35% for the composite endpoint combining 90 day mortality and PA-VAP recurrence as shown in a previous study [7]. This expected rate is in accordance with previously published data. Hence, Combes et al. reported a recurrence rate of 28% [22]. In a meta-analysis, the frequency of VAP recurrence was 26.8%. Acute lung injury/acute respiratory distress syndrome and shock on the day of diagnosis of the first VAP episode, but not the first-episode causative pathogens, were found to be associated with VAP recurrence [23]. Finally, in the cohort published by Planquette et al. on 314 patients with 393 PA-VAP, failure occurred for 112 of them (35.7%), including 79 recurrences (20.1%) [7].

Crouch Brewer et al. reported in a cohort of 38 consecutive PA-VAP a mortality of 69% with an attributable mortality of 38% [4]. We can emphasize that persistent pneumonia occurred in 35% of patients while recurrence of pneumonia was unusual (1/38). Trouillet at al. reported a cohort of 135 PA-VAP. In this cohort, 70 patients (52%) died during the ICU stay, and only 10 patients had recurrences [5]. Finally, in a retrospective, multicenter, observational cohort study conducted in five Spanish ICUs, Garnacho-Montero et al. reported 183 monomicrobial episodes of PA-VAP, with a mortality of 42.1% [6], and an Italian retrospective analysis of data prospectively collected about 110 cases of PA-VAP and reported an ICU mortality of 44.5% [24].

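### Non-inferiority is decided on a per-protocol set selected by antibiotic duration received, with no requirement that ITT agree, so the primary comparison can be biased in either direction

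*Protocol article*

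**What the plan says.** The Data analysis section of the protocol article fixes the decision set: "Since this is a non-inferiority study, analysis of principal criteria will be performed on a per protocol population". Among the major deviations that remove a patient it lists "clear non-respect of the antibiotic duration allocated (+/– 24 hours), missing data for the primary endpoint", and it adds "major protocol deviation(s) identified during a blinded data review before data base freezing". The other population appears in one sentence: "Secondary analysis in an intent-to-treat (ITT) population will also be performed". Nothing there requires the two analyses to agree before non-inferiority is claimed.

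Three other places bear on this.

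- The Study population section has all antibiotics withdrawn at the end of day 8 or day 15 according to allocation, "except those prescribed for a documented pulmonary infection recurrence or a new extrapulmonary infection before that day". It also places randomization just after the susceptibility results, so before either stop.
- Assessment criteria defines the primary endpoint as death by day 90 and/or PA-VAP recurrence in the ICU.
- The Discussion describes the short arm as "8 days of effective antibiotic therapy" and names non-compliance with duration as a risk of the open-label design.

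**The concern.** In this trial the duration is the intervention, and the per-protocol set is selected on the duration actually received. That variable arises after randomization, and death and clinical course can both determine it. With a 24-hour tolerance, compliance needs survival and treatment to about day 7 in SD and about day 14 in LD. The filter is therefore not the same in the two arms, even if the strategies are equally good.

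There are three routes, with different signs:

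- If death on allocated treatment counts as a duration deviation, a death on day 11 stays in SD as an event but leaves LD. This works against SD.
- If SD patients doing badly at day 8 are continued open-label and then excluded, events leave SD. This favours non-inferiority.
- If LD patients doing well are stopped early and excluded, non-events leave LD. This also favours non-inferiority.

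At stake is the trial's single primary conclusion. A truly non-inferior short course could be missed, or an inferior one accepted, and a discordant ITT result would not formally prevent the claim.

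**Working it through.** **Inputs from the article (Statistical analysis section).** Event rate 35.7%, margin 10 points, alpha 5% (sidedness not stated), power 80%, 284 per group, 600 enrolled to allow for 5% loss to follow-up.

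**The plan's own figure.** n = (1.645 + 0.842)² × 2 × 0.357 × 0.643 / 0.10² = 284 per group, which matches if alpha is one-sided 5%. At one-sided 2.5% the formula gives 361. Then 284/0.95 = 299 per arm, 598 in all, rounded to 600. With 300 per arm less 5%, 285 remain and power is 80.1%. The 5% is for loss to follow-up; no allowance is made for per-protocol exclusions.

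**Assumptions.** The article gives no exclusion or death-timing rates. The shares x and y below are chosen for illustration.

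**Formulas.** If a share x of an arm is removed and all of them had an event, the per-protocol rate is (p − x)/(1 − x). If a share y is removed and none had an event, it is p/(1 − y). The probability of declaring non-inferiority is Φ[(0.10 − d)/SE − 1.645], where d is the per-protocol difference SD − LD and SE is the unpooled standard error with 285 per arm less the exclusions.

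**(a) Extra events lost from LD, arms truly identical at 35.7%.**

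| x | LD rate | Shift in SD − LD | Power |
|---|---|---|---|
| 1% | 35.05% | +0.65 | 75% |
| 3% | 33.71% | +1.99 | 64% |
| 5% | 32.32% | +3.38 | 50% |

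Worked line for 5%: (0.357 − 0.05)/0.95 = 0.3232. SE = √(0.357 × 0.643/285 + 0.3232 × 0.6768/270.75) = 0.0402. Then (0.10 − 0.0338)/0.0402 − 1.645 ≈ 0, so power is 50%.

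As a check on plausible values, take randomization on day 3, 90-day mortality of 15-35%, and a hazard that is constant or front-loaded (Weibull shape 0.6), and count death before day 7 (SD) or day 14 (LD) as a deviation. SD then loses 0.7-3.6% of patients and LD 2.0-8.2%, and the per-protocol difference is +0.8 to +3.3 points when the truth is zero.

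**(b) Events lost from SD, true excess 10 points (45.7% v 35.7%).**

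| x | SD rate | Per-protocol difference | False non-inferiority |
|---|---|---|---|
| 1% | 45.15% | 9.45 | 6.5% |
| 3% | 44.02% | 8.32 | 10.8% |
| 5% | 42.84% | 7.14 | 17.0% |

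**(c) Well LD patients stopped early and excluded.** With y = 2%, 5% or 10%, the LD rate rises from 35.7% to 36.4%, 37.6% or 39.7%. The shift is −0.7, −1.9 or −4.0 points, and false non-inferiority at a true 10-point excess is 7.1%, 11.6% or 23.9%.

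**(d) Equal event losses in arms with equal rates.** The shift is zero.

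**The case against.** A per-protocol primary analysis is a familiar choice in non-inferiority trials, an ITT analysis is planned, and the article condenses a fuller protocol and an analysis plan that are not shown. The deviation list is introduced as examples, so exemptions may well be spelled out there. This stands for the detail of the exemptions. It does not stand for the choice of decision set, which the article states outright.

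A reader might infer more than the text supports in four respects.

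- *That the comparison is biased.* The routes have opposite signs and may partly cancel; the article fixes neither direction nor size.
- *That deaths are removed.* The criterion is "clear non-respect of the antibiotic duration allocated", and a patient who dies while on allocated treatment has not plainly disregarded it. Exclusion is one reading of a silent text.
- *That recurrences are removed from LD.* A recurrence on day 11 treated beyond day 15 falls within the antibiotics that the Study population section permits, so it is not naturally a major deviation.
- *That the effect is very large.* If 5% die before the first stop and 4-8% between the stops, the per-protocol rates are (0.357 − 0.05)/0.95 = 32.3% in SD and 29.3-26.1% in LD. That is +3.0 to +6.2 points, with power of 54-24%. The arithmetic is right, but it needs 9-13% dead by the day-15 stop. In the cohort behind the 35.7%, the Discussion gives 112 failures among 314 patients, including 79 recurrences. If both counts are per patient, only 33/314 = 10.5% failed without recurrence over the whole follow-up. The 20.1% for recurrences is per episode (79/393), so the units are unclear. Other cohorts cited there report higher mortality. These inputs are possible, but they should not be presented as the expected case.

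Two side issues do not carry the point. The plan says "Missing data will be not replaced", but repeated contact attempts and civil records are planned for vital status, and imputation is ordinary analysis-plan content. Blinded data review and blinded assessment of recurrence are real safeguards against deliberate selection. They do not alter what a duration rule itself selects.

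**Conclusion.** The concern holds in this form: the decision rests on a set defined by duration received, compliance is reached about a week later in LD than in SD, and ITT is not required to agree. The comparison can therefore be biased, in either direction.

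The illustrations assume 285 per arm, one-sided 5% alpha and exclusion shares that are not in the article. An extra 1-5% of LD patients, all with events, moves the difference by +0.65 to +3.4 points and lowers power to 75-50%. The same losses from SD raise false non-inferiority to 6.5-17%. Early stops in 2-10% of well LD patients raise it to 7.1-23.9%. These figures show sensitivity to small differential exclusions; they are not estimates of what will happen. The concern is a weakness in the decision rule, not a demonstrated bias.

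**What to change.** 1. Make ITT (all randomized patients, as allocated) co-primary with per-protocol, and claim non-inferiority only if the upper confidence bound for SD − LD is below 10 points in both.
2. State that, for the per-protocol set, neither death on allocated treatment nor antibiotics already permitted in the Study population section is a duration deviation.
3. Reconcile the Abstract and Discussion, which count days of effective therapy, with the Study population section, which refers to the end of day 8 or day 15, so that the 24-hour tolerance is measured on one clock. Which clock applies is for the investigators to settle.

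All three should be settled before the database is frozen. They change wording only and need no new data.

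The cost is slightly lower joint power, because both analyses must succeed. ITT with 285 per arm has 80.1% power. Joint power cannot exceed the per-protocol figure, which even under purely random exclusion falls to 78.2%, 73.9% or 68.9% if 10%, 20% or 30% of the 300 per arm are excluded in all.

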**Methods/design:**

The impact of the duration of antibiotics on clinical events in patients with *Pseudomonas aeruginosa* ventilator-associated pneumonia (iDIAPASON) trial is a randomized, open-labeled non-inferiority controlled trial, conducted in 34 French intensive care units (ICUs), comparing two groups of patients with PA-VAP according to the duration (8 days or 15 days) of effective antibiotic therapy against PA. The primary outcome is a composite endpoint combining day 90 mortality and PA-VAP recurrence rate during hospitalization in the ICU. Furthermore, durations of mechanical ventilation and hospitalization, as well as number and types of extrapulmonary infections or acquisition of MDR pathogens during the hospitalization in the ICU will be recorded. Recurrence with predefined criteria (clinical suspicion of VAP associated with a positive quantitative culture of a respiratory sample) will be evaluated by two independent experts.

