**Fig. 1 Fig1:**
[figure not shown]
Conduct of the study. Study protocol flowchart. *SAPS* 2: Simplified acute physiology score II; *SOFA:* Sequential organ failure assessment; *CPIS:* clinical pulmonary infection score

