[name] (chair)	CHU La Pitié-Salpêtrière, Paris
[name]	CHU La Pitié-Salpêtrière, Paris
[name]	URC-Est, Paris
[name]	CH Chartres
[name]	CHU Beaujon, Paris
[name]	CHU Amiens
[name]	Hôpital Européen Georges Pompidou, Paris
[name]	CHU Clermont-Ferrand
[name]	Hôpital Nord, Marseille
[name]	CHU Bichat, Paris
[name]	CHU Bordeaux
[name]	Clinique Ambroise Paré, Neuilly-sur-Seine
[name]	CHU Rouen

The study will be performed in 39 French adult ICUs (Table 1). This work is supported by institutional grants from the French 2014 Programme Hospitalier de Recherche Clinique National (PHRC P140923 – AOM14515). The study is sponsored by the Clinical Research and Development Department of Assistance Publique – Hôpitaux de Paris. The sponsor had no role in the study design, collection, management, analysis, or interpretation of data, writing of the report, or the decision to submit the report for publication. The total duration of the study will be 27 months, including the inclusion period (24 months) and the duration of participation per patient (90 days).

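### Randomisation is stratified by centre but the named primary test is unstratified and unadjusted: valid and adequately powered as planned, but it forgoes precision that a change of wording could recover

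*Protocol article*

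**What the plan says.** Protocol article, Randomization: allocation is "Centralized blocked-balanced randomization, in a 1:1 ratio", and "Randomization will be stratified on center". The Abstract gives 34 ICUs, while the Methods text by Table 1 says "The study will be performed in 39 French adult ICUs".

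Protocol article, Data analysis: "Non-inferiority will be tested by a Dunnett and Gent chi-squared procedure". The primary population is per protocol, with intention to treat secondary. The only models with an adjustment term in that section are exploratory logistic regressions, and they adjust for randomisation group.

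Protocol article, Statistical analysis: the expected event rate is 35.7%, and the aim is "to exclude a 10% difference between the two groups" with 80% power and 5% alpha. This gives 284 per group, raised to 600 in total for 5% loss to follow-up.

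SAPS II, SOFA and CPIS appear in the legends to Figs. 1 and 2 (for example "Simplified acute physiology score II"). The primary analysis does not use them.

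**The concern.** Blocking within centre keeps the arms nearly balanced in each ICU. If ICUs differ in mortality or recurrence, that balance removes between-centre variation from the sampling error of the risk difference. A single pooled 2×2 table still counts this variation, so its standard error is larger than the design warrants. A prognostic baseline score is a second, separate source of precision that the analysis leaves unused.

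What is at stake is efficiency. The margin for attrition is thin: 600 × 0.95 = 570 patients against 2 × 284 = 568 required. The per-protocol definition also removes patients who depart from the allocated duration by more than 24 hours or who have other major deviations, and the Discussion accepts that non-compliance is a particular risk of the open design. These exclusions are not in the sample size. Precision recovered in the analysis would offset some of them.

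**Working it through.** **Inputs.** From the article: p = 0.357 in both arms, margin 0.10, 80% power, alpha 5%, 284 per arm, 34 or 39 centres. Assumed, because the documents do not give it: R², the share of outcome variance explained by centre and/or severity.

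**1. Reproduce the plan's figure.** n = (z₀.₉₅ + z₀.₈₀)² × 2p(1−p) / 0.10² = (1.645 + 0.842)² × 0.4591 / 0.01 = 283.8, so 284. This matches. A one-sided 2.5% level gives 361, which does not, so one-sided 5% is inferred; the article does not state sidedness. SE = √(0.4591/284) = 0.0402, and power = Φ(0.10/0.0402 − 1.645) = 80.0%. With the Dunnett and Gent null-constrained variance, power is 80.3%. The sample size was therefore set for an unadjusted comparison.

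**2. Centre, by formula.** With balance inside centres, the true SE is 0.0402 × √(1−R²), and the crude SE is too large by the factor 1/√(1−R²). The crude test also benefits in part, because its estimate varies less than its SE implies: its power is Φ((0.10 − 1.645 × 0.0402) / (0.0402√(1−R²))). Between-centre SD is on the logit scale.

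| Centre SD | R² | Crude SE too large by | Crude power | Stratified power |
|---|---|---|---|---|
| 0.3 | 2.0% | 1.0% | 80.3% | 80.7% |
| 0.5 | 5.2% | 2.7% | 80.7% | 81.9% |
| 0.8 | 11.7% | 6.4% | 81.5% | 84.2% |

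Against the planned 80%, the centre gain is about 1 to 4 points. Head to head with the crude test in the same stratified trial it is 0.4, 1.2 and 2.7 points.

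**3. Centre, by simulation.** Set-up: 568 patients, 34 unequal centres, blocks of 4 (assumed), 2,500 runs per setting.

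| Centre SD | Crude mean SE / true SD | Crude power | Mantel-Haenszel power |
|---|---|---|---|
| 0 | 0.0401/0.0392 | 81.0% | 80.4% |
| 0.3 | 0.0401/0.0395 | 81.1% | 81.1% |
| 0.5 | 0.0401/0.0395 | 80.2% | 80.8% |
| 0.8 | 0.0400/0.0374 | 82.5% | 84.9% |

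Where centres differ, the SE ratios are 1.015, 1.015 and 1.070. The first row shows the noise: with no centre effect the ratio is still 1.023, and the Monte Carlo error of a simulated SD is about 1/√5000 = 1.4%. The first row also shows that stratifying costs about 0.6 points when centres do not differ.

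**4. Centre plus severity.** For logit SDs (centre/severity) of 0.3/0.5, 0.5/0.8 and 0.5/1.0, crude power was 79.8%, 81.8% and 81.5%. Power adjusted for both was 82.2%, 86.4% and 86.5%. That is about 2 to 7 points above the planned 80%, and 2.3, 4.6 and 5.0 points head to head.

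**5. Type I error.** With a true difference of 10 points, the crude test rejected in 3.8% to 5.6% of runs across all settings, and Mantel-Haenszel in 4.1% to 5.6% (Monte Carlo error about 0.4 points). Neither shows material inflation.

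**6. Per-protocol attrition.** Suppose 15% of 600 are excluded (an assumption), leaving 255 per arm. Then SE = √(0.4591/255) = 0.0424 and power = 76.2%. If adjustment explains R² = 10% (an assumption), SE = 0.0424 × √0.9 = 0.0403 and power = 79.9%.

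**The case against.** The strongest defence is that the test and the sample size agree. The trial was sized for an unadjusted comparison, and that comparison delivers 80%. The mismatch with the stratified design errs on the safe side: it cannot manufacture a false non-inferiority claim. All of that stands.

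It is also fair that no ICC or R² is documented, that the centre gain is under about 1 point unless centres differ noticeably, and that 568/39 = 14.6 to 568/34 = 16.7 patients per centre makes some strata sparse or one-armed. For severity, the documents show only abbreviations in figure legends. Whether the scores precede randomisation, which follows the susceptibility results, cannot be seen. The Discussion links shock and acute lung injury at the first episode to recurrence, but it does not say that SAPS II or SOFA predict the composite. A model needing complete scores could also lose patients, since Data analysis says missing data are not replaced.

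A further defence is that an unseen SAP may add stratified analyses. It may, but the article itself names the confirmatory test, so a supporting analysis elsewhere would not change which result decides the trial.

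Three stronger readings are tempting, and the documents do not support them:
- **That planned power is lost.** It is not: 284 per arm reproduces for the unadjusted test. Only additional power is forgone.
- **That leaving out SAPS II or SOFA makes the standard error wrong.** They are not stratification factors, so the crude SE remains valid and already reflects chance imbalance in severity. Omission costs efficiency only.
- **That a chi-squared procedure cannot support a non-inferiority claim.** A test against a non-zero margin corresponds to a one-sided confidence bound.

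**Conclusion.** The point holds as a modest matter of efficiency and is not a validity defect. The primary analysis does not use the strata in which patients were randomised. If centres differ, its SE is about 1% to 7% too large, in the conservative direction. Relative to the planned 80%, about 0 to 4 power points are available from centre and about 2 to 7 if a baseline severity score is added. Head to head with the named test, the simulated gains are smaller: 0 to 2.4 points for centre and 2.3 to 5.0 for both.

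These figures rest on assumed between-centre SDs of 0.3 to 0.8 and severity SDs of 0.5 to 1.0 on the logit scale, an inferred one-sided 5% level, and 284 evaluable patients per arm. The case for acting is that the change is cheap and per-protocol exclusions beyond the 5% allowance are likely to use up the small reserve.

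**What to change.** Before any unblinded look at outcomes, restate the primary analysis as a centre-stratified Mantel-Haenszel risk difference with its one-sided 95% upper bound, compared with the unchanged 10-point absolute margin. State the one-sided level explicitly. Pre-set the rule for pooling small or one-armed centres without reference to outcomes. Keep the Dunnett and Gent test as a sensitivity analysis.

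Optionally, standardise the risk difference for one pre-specified severity score as well, provided the score is measured before randomisation and a stated rule keeps patients with a missing score in the analysis.

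The cost is wording, code, a pooling rule and slightly more analysis work. It needs no extra patients. If centres turn out not to differ, the price is a fraction of a power point (about 0.6 in the simulation).

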### Assessment criteria

The primary assessment criterion will be a composite endpoint combining day 90 mortality and PA-VAP recurrence rate during hospitalization in the ICU (within 90 days). Recurrence will be defined with a post hoc analysis by two independent experts with predefined criteria: clinical suspicion of VAP (≥ two criteria including: fever >38.5 °C, leukocytosis >10^9^/L or leukopenia <4.10^8^/L, purulent tracheobronchial secretions, and a new or persistent infiltrate on chest radiography) associated with a positive quantitative culture of a respiratory sample (bronchoalveolar lavage fluid (significant threshold ≥10^4^ CFU/mL), plugged telescopic catheter (significant threshold ≥10^3^ CFU/mL), or quantitative endotracheal aspirate distal pulmonary secretion samples (significant threshold ≥10^6^ CFU/mL)). In cases of disagreement between the two experts, a third expert will reach a consensus. Thereby, the percentage of patients with PA-VAP recurrence and/or death will be assessed.

Secondary assessment criteria will be 30 day and 90 day mortality rate, PA-VAP recurrence rate, mechanical ventilation (MV)-free days, ICU-free days, antibiotic-free days during the hospitalization in the ICU, number and types of extrapulmonary infections during the hospitalization in the ICU, and acquisition of MDR pathogens during the hospitalization in the ICU (from swab sample of rectum and anterior nares).

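### Three secondary outcomes are listed as free days but tested as raw durations, with no rule for patients who die

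*Protocol article*

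**What the plan says.** The Assessment criteria section names the secondary outcomes. It begins "Secondary assessment criteria will be 30 day and 90 day mortality rate, PA-VAP recurrence rate" and goes on to "mechanical ventilation (MV)-free days, ICU-free days, antibiotic-free days during the hospitalization in the ICU", followed by extrapulmonary infections and acquisition of MDR pathogens.

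The Data analysis section opens its secondary part with "Secondary outcomes will be analyzed under a superiority assumption" and then assigns tests:

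- Binary outcomes: "Day 30 and day 90 mortality rates and acquisition of MDR pathogens during hospitalization in the ICU will also be compared between groups", by chi-squared or Fisher's exact test.
- Continuous outcomes: "Duration of mechanical ventilation, duration of hospitalization in the ICU, duration of exposure to antibiotics", together with the number of extrapulmonary infections, "will be compared between groups by Student *t* tests or Mann-Whitney/Wilcoxon tests, if needed".

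Free days are not mentioned in Data analysis, and no rule is given for a patient who dies on the ventilator, in the ICU or on antibiotics. The abstract and the secondary objectives also speak of durations. Recurrence appears in Data analysis only as an outcome of prognostic models, for example "respiratory colonization with yeast at diagnosis and PA recurrence will be studied by logistic regression adjusted on the randomization group".

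**The concern.** Two sections of one article each fix a variable for the same three outcomes, and the variables differ. A fuller document may add detail, but it cannot make both statements true.

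The difference is one of substance. A free-day count scores a death as a bad result. A raw duration, without a rule to the contrary, ordinarily stops at death and so scores an early death as a short stay. The Background section cites mortality of 40% to 69% for this pneumonia, so many patients would be affected. If the short-course arm had more early deaths, the analysis as written could show it leaving the ventilator and the ICU sooner. The trial is also open-label, and with both variables on record the choice between them could be made after results are known.

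**Working it through.** **Step 1: match each listed criterion to its analysis.**

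| Criterion listed | What Data analysis does |
|---|---|
| 30- and 90-day mortality | chi-squared or Fisher: matches |
| PA-VAP recurrence rate | no between-arm comparison named |
| MV-free days | duration of ventilation tested instead |
| ICU-free days | duration of ICU stay tested instead |
| Antibiotic-free days | duration of exposure tested instead |
| Number of extrapulmonary infections | t or Wilcoxon: matches |
| Types of extrapulmonary infections | described: matches |
| MDR acquisition | chi-squared or Fisher: matches |

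Four of eight match, three are replaced by a different variable, and one has no named between-arm test.

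**Step 2: the plan's own figure.** The point disputes no stated number. The sample size reproduces at one-sided 5%: n = (1.645 + 0.842)² × 2 × 0.357 × 0.643 / 0.10² = 283.8, so 284 per arm. Then 568 / 0.95 = 598, rounded to 600. It plays no part in the concern except as the arm size below.

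**Step 3: can the two variables disagree?** These inputs are assumptions, not figures from the article. The time on ventilation that would be needed is exponential with mean 15 days in both arms, capped at day 90. A fraction m of patients die, at times uniform over days 0 to 30. Raw duration ends at death. Free days run to day 90, with death scored as 0.

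- Mean raw duration in survivors: 15 × (1 − e⁻⁶) = 14.96 days.
- Mean raw duration in patients who die: 15 − 7.5 × (1 − e⁻²) = 8.52 days.
- Mean raw duration in the arm: 14.96 × (1 − m) + 8.52 × m.
- Mean free days in the arm: (90 − 14.96) × (1 − m) = 75.04 × (1 − m).

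For m = 0.30 the raw mean is 10.47 + 2.55 = 13.0 days, and for m = 0.20 it is 11.97 + 1.70 = 13.7. Free days are 52.5 and 60.0. Each extra 10 points of mortality shortens the raw mean by 0.64 day and removes 7.5 free days.

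Simulated trials with 284 per arm (2,000 runs each, Mann-Whitney at two-sided 5%) gave these shares of trials:

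| Mortality, arm A vs arm B | Raw duration: A significantly worse | Raw duration: A significantly better | Free days: A significantly worse |
|---|---|---|---|
| 20% vs 20% | 2.9% | 3.0% | 2.0% |
| 25% vs 20% | 1.5% | 3.9% | 18% |
| 30% vs 20% | 0.4% | 7.2% | 56% |
| 45% vs 35% | 0.5% | 8.0% | 57% |

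With equal mortality neither measure shifts beyond chance.

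**Step 4: a second model.** Ventilation need is gamma (shape 2, scale 8 days), deaths occur at 1 day plus an exponential time with mean 9 days, and free days run to day 28.

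- Mortality 25% vs 32%: raw duration 13.8 vs 13.2 days; free days 10.2 vs 9.3.
- Mortality 40% vs 47%: raw duration 12.5 vs 11.9 days; free days 8.3 vs 7.4.

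The sign reverses again. With deaths spread uniformly over 90 days and mortality 25% vs 32%, the raw gap falls from about 0.6 to about 0.2 day and the free-day gap from about 0.9 to about 0.3. The direction stays and the size shrinks.

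**The case against.** The strongest reply is that Data analysis agrees with the abstract and the objectives, so the free-day sentence is the outlier, and that scoring of deaths and the time horizon are ordinary content of an analysis plan that is not shown. That is fair as to missing detail. It does not remove a conflict between two variables that are both stated.

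A second reply is that the sizes rest on invented inputs. This stands. In the second model the raw gap of about 0.6 day has a standard error of about 0.9 day at 285 per arm, which gives roughly 11% power. A significant false benefit would therefore be uncommon. The more likely harm is that the raw durations fail to show a disadvantage that free days would show. Free days, for their part, mix death with time on support. In these illustrations the whole free-day difference comes from mortality.

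A reader might also infer more than the article supports:

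- *That recurrence is not analysed at all.* It is modelled in logistic regressions adjusted for arm and in the procalcitonin analyses. Only a named between-arm comparison is absent, and the full protocol or SAP may supply one.
- *That the claim of no excess mortality or recurrence will rest on non-significant superiority tests.* The article does not say so. That aim is addressed by the primary non-inferiority test on the composite of those two events.
- *That confining antibiotic-free days to the ICU stay is an error.* It is a stated scope.
- *That the article says durations are truncated at death.* It is silent. Truncation is the ordinary consequence of having no rule.

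**Conclusion.** The mismatch is real for three secondary outcomes and can be seen by setting the two sections side by side. Following Data analysis as written can favour the arm with more early deaths, while the criteria listed under Assessment criteria, with death scored as zero, would not. In the first illustration, 10 extra points of mortality move mean ventilation time by about 0.6 day in the flattering direction and ventilation-free days by 7.5 in the other. These figures assume equal ventilation need, early deaths and durations that end at death. They shrink with later deaths and vanish with equal mortality. The conflict should be resolved before the data are analysed, but it bears on secondary conclusions only. The primary endpoint, its test and the sample size stand.

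**What to change.** In Data analysis, replace the three raw durations with the free-day criteria already listed. Count them from randomisation to one fixed day, score death by that day as 0, and compare arms by Wilcoxon test. Say how days after ICU discharge count, in particular for antibiotic-free days, whose scope is the ICU stay. Align the wording of the abstract and the objectives. Raw durations can be kept as description, for example in survivors, read with the caution that survivors are a group selected after randomisation.

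As a minor addition, report the between-arm risk difference with a confidence interval for PA-VAP recurrence and for day-90 mortality beside the composite, so that opposite movements in the two components can be seen.

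The cost is analysis wording. Vital status to day 90 is already needed for the primary endpoint, and the dates behind the durations are already needed for the comparisons now planned. No change to sample size or conduct follows.
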